## Abstract

**Background::**

External lumbar drainage (ELD) remains the most common used methods with a higher sensitivity before lumboperitoneal shunt (LPS) implantation to predict the shunt outcomes in the treatment of idiopathic normal pressure hydrocephalus. However, the benefits of such supplemental test have not been tested in the treatment of post-hemorrhagic hydrocephalus (PHH).

**Methods and design::**

In the current trial, 100 eligible patients with PHH will be recruited and randomly assigned to the ELD group (study group) and non-ELD group (control group). Lumbar puncture (LP) will be performed for participants in non-ELD group. LP plus ELD will be performed for participants in ELD group, those who will then be investigated the suitability of potential LPS 4 days after ELD. Two independent and practiced assessors will collect the baseline data and evaluate each participant 4 days after ELD or LP, 1 day after LPS, at the time of discharge and 1 month after LPS. The primary outcome is the shunting outcomes 1 month after surgery. The secondary outcomes include the complications related to ELD, complications related to LPS, and Evens index at each evaluation point. Meanwhile, serious adverse events occurring at any time is recorded to determine the safety of this trial.

**Discussion::**

The results of this trial will demonstrate whether preoperative evaluation using temporary ELD for patients with PHH could attenuate the risk of LPS failure.

**Trial registration number:**

ChiCTR2000034094; Pre-results.

## Introduction

1

Since the application of shunt surgery in clinic, a great deal of attention was directly given to quest the path to attenuate the incidence of shunt failure.^[1,2]^ To date, preoperative accurate evaluation through supplemental test has been widely accepted to correctly select the suitable patients for shunt implantation.^[3,4]^ In this regard, external lumbar drainage (ELD) remains the most common used methods with a higher sensitivity before lumboperitoneal shunt (LPS) implantation to predict the shunt outcomes in the treatment of idiopathic normal pressure hydrocephalus.^[5]^ However, the benefits of such supplemental test have not been tested in the treatment of post-hemorrhagic hydrocephalus (PHH), a common disease occurring secondary to intracranial hemorrhage.^[6]^

## Methods and design

2

### Objective

2.1

To prove whether preoperative evaluation using ELD for patients with PHH could attenuate the risk of LPS failure.

### Study design

2.2

The flow chart of the selection of patients is shown in Figure 1. In the current trial, 100 eligible patients with PHH will be recruited from the Department of outpatient of Sichuan University West China Hospital since September 1, 2020, and randomly assigned to the ELD group (study group) and non-ELD group (control group). Lumbar puncture (LP) will be performed for participants in non-ELD group. LP plus ELD will be performed for participants in ELD group, those who will then be investigated the suitability of potential LPS 4 days after ELD. Two independent and practiced assessors will collect the baseline data and evaluate each participant 4 days after ELD or LP, 1 day after LPS, at the time of discharge and 1 month after LPS. The primary outcome is the shunting outcomes 1 month after surgery. The secondary outcomes include the complications related to ELD, complications related to LPS, and Evens index at each evaluation point. Meanwhile, serious adverse events occurring at any time is recorded to determine the safety of this trial.

**Figure 1 F1:**
[figure not shown]
Flow chart of the selection pf patients. CSF = cerebrospinal fluid, ELD = external lumbar drainage, GCS = Glasgow coma scale, ICH = intracranial hemorrhage, LPS = lumboperitoneal shunt, mRS = modified Rankin Scale, NIHSS = National Institute of Health stroke scale.

### Recruitment and eligibility

2.3

#### Inclusion criteria

2.3.1

1.Age >18 years;2.Ventricular expansion occurring secondary to intracranial hemorrhage;3.Evans index >0.3;4.LP indicates that the subarachnoid space of spinal cord is connected with ventricles, and the cerebrospinal fluid opening pressure is between 70 and 200 mm Hg.

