#### Exclusion criteria

2.3.2

1.Obstructive hydrocephalus;2.Decline to ELD or LPS surgery;3.Skull defect.

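### Inclusion criterion 4 sets the CSF opening pressure at 70 to 200 mm Hg, an implausible range for this population; the printed unit appears wrong and must be verified

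*Protocol article*

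**What the plan says.** Section 2.3.1 of the protocol article (Inclusion criteria) lists four requirements. The fourth has two parts, both established by lumbar puncture. The first is that "LP indicates that the subarachnoid space of spinal cord is connected with ventricles". The second is that "the cerebrospinal fluid opening pressure is between 70 and 200 mm Hg". This is the only numerical pressure limit in the text shown, and no other section restates it, gives it in another unit or corrects it. Figure 1, the patient-selection flow chart, is not visible, so it cannot be compared.

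Four other parts of the article describe who these patients are:

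- Section 2.2 (Study design): the patients "will be recruited from the Department of outpatient of Sichuan University West China Hospital".
- Section 2.3.2 (Exclusion criteria): "1.Obstructive hydrocephalus;2.Decline to ELD or LPS surgery;3.Skull defect". With the first part of criterion 4, this restricts the trial to communicating hydrocephalus.
- Section 1 (Introduction): lumbar drainage is described as a test used "to predict the shunt outcomes in the treatment of idiopathic normal pressure hydrocephalus". The trial carries that test over to hydrocephalus after hemorrhage.
- Sections 2.2 and 2.7: all participants have a lumbar puncture, and the study arm also has a lumbar catheter for temporary drainage.

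**The concern.** A range of 70 to 200 mm Hg is where one expects arterial blood pressures. It does not fit a lumbar CSF reading in outpatients with open CSF pathways who are being assessed with a test borrowed from normal pressure hydrocephalus. The numerals look like a manometer reading in a smaller unit with the wrong unit printed after them.

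The pressure limit is a condition of entry, so it decides who is in the trial. Applied literally, it would exclude essentially every plausible participant. If it is quietly read in another unit, the enrolled patients may not meet the published criterion. Eligibility could then not be checked against the text, and another group could not reproduce the population. Section 2.10 has all data recorded both on paper and by electronic capture, so a wrong unit could also pass into a field label or a range check.

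**Working it through.** There is no plan calculation to reproduce: the range is a fixed criterion, not a result derived from other inputs. The check is a unit conversion followed by a comparison with the article's own description of the patients.

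**Inputs**

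- Lower and upper limits of 70 and 200, with the unit printed as mm Hg: protocol article, section 2.3.1, criterion 4.
- Physical constants, not from the article: 1 mm Hg = 133.322 Pa and 1 mm H2O = 9.80665 Pa.

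**Step 1: conversion factor**

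133.322 / 9.80665 = 13.595, so 1 mm Hg = 13.595 mm H2O.

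**Step 2: the criterion as printed, in mm H2O**

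- Lower limit: 70 × 13.595 = 952 mm H2O (95 cm H2O).
- Upper limit: 200 × 13.595 = 2,719 mm H2O (272 cm H2O).

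This is a water column of about 0.95 to 2.7 metres.

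**Step 3: the same numerals under other units**

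The article does not give the intended unit, so these are assumptions.

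| Assumed unit of 70 to 200 | Lower limit, mm Hg | Upper limit, mm Hg | Overlaps 70 to 200 mm Hg? |
|---|---|---|---|
| mm Hg (as printed) | 70 | 200 | same range |
| mm H2O | 70 / 13.595 = 5.1 | 200 / 13.595 = 14.7 | no |
| cm H2O | 700 / 13.595 = 51.5 | 2,000 / 13.595 = 147.1 | yes |

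Under mm H2O the highest admissible pressure, 14.7 mm Hg, lies well below the lowest printed one, 70 mm Hg. No pressure satisfies both readings. Under cm H2O the range still reaches arterial values, so that reading does not remove the difficulty.

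**Step 4: comparison with the rest of the article**

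Outpatient recruitment, communicating hydrocephalus, routine lumbar puncture and a test taken from normal pressure hydrocephalus all point to pressures far below the printed range. Nothing in the article supports a CSF pressure of 70 mm Hg or more.

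**The case against.** The strongest reply is that an implausible unit does little practical harm. Section 2.6 provides for central training of the clinical staff beforehand. The further the printed figure is from reality, the less likely it is that a neurosurgical team would act on it; they would probably read the manometer in its usual unit and apply the numerals to that. The slip does not touch randomisation, the primary outcome, the sample size or the analysis. The article is also a condensed account. The full protocol and the case record form may carry the right unit, and Figure 1 cannot be seen.

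Much of this stands. It makes direct harm unlikely and leaves open how far the error extends. It does not rescue the criterion itself: the article states a unit in full, and the rule it states cannot be used.

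A reader might also infer several stronger things that the article does not support:

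- **That the threshold is 13.6 times too high.** This holds only if mm H2O was meant and the numerals are right. The article says neither.
- **That all of the intended patients would fail.** The article gives no intended range and no pressure distribution, so no such percentage can be derived from it. The non-overlap is a consequence of the mm H2O assumption.
- **That patients with dangerously raised pressure would be sent for drainage.** This requires trained staff to apply the range literally, which is improbable.
- **That different sites may use different units.** The Discussion describes a single-center study, so variation between sites cannot arise.
- **That the patients are ambulatory.** Outpatient recruitment does not establish this.

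**Conclusion.** The point holds as a unit error in a binding eligibility criterion. As printed, criterion 4 requires about 952 to 2,719 mm H2O, which is not plausible for the patients the article describes. That conclusion rests on the conversion constant and on general knowledge that such values are arterial rather than lumbar CSF pressures. It does not depend on knowing the intended unit.

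The size of the discrepancy does depend on the unit. On the assumption of mm H2O, the numerals mean 5.1 to 14.7 mm Hg, the two ranges are disjoint, and every patient enrolled under that reading would formally be outside the written criterion.

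The consequence is chiefly one of audit and reproducibility, with a possible knock-on to the data forms and checks. It is not a demonstrated risk to patients or a bias in the comparison between arms. The point still merits correction because the rule decides entry to the trial and cannot be followed as it stands.

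**What to change.** Check the unit of criterion 4 against the full protocol, the case record form, Figure 1 and the scale of the manometer in use, and reconcile section 2.3.1 with what they show. Then state one unit consistently in the criterion, on the paper form, in the electronic data capture field and in its range check. If patients have already been screened, record which unit was applied to them. The choice of limits and unit belongs to the sponsor and the investigators; no threshold is proposed here.

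The cost is small: a check of existing documents, a short wording amendment if the error is confirmed, and an adjustment to the field label and edit check where they carry it. The design, sample size and analysis do not change.

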#### Exclusion criteria

2.3.2

1.Obstructive hydrocephalus;2.Decline to ELD or LPS surgery;3.Skull defect.

### Sample size

2.4

Previously published reports indicated that the rate of LPS failure for patients with preoperative evaluation using ELD was 15.7%, comparing with a rate of 40.9% for patients without ELD.^[7]^ In this regard, a sample of 45 will be required in this trial with a significance level of 5% (2-sided) and a power of 80% to demonstrate a 20% difference in rate of shunt failure. Considering about the loss to follow-up, the sample size is enlarged to 50 for each group.

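### Section 2.4 claims 80% power for a 20-point difference with 45 per group; the quoted rates give about 54–61%, and the 20% target is the likely slip

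*Protocol article*

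**What the plan says.** Everything on this point stands in the protocol article, section 2.4 (Sample size). It cites earlier reports in which "the rate of LPS failure for patients with preoperative evaluation using ELD was 15.7%, comparing with a rate of 40.9% for patients without ELD". The next sentence rests on those rates and gives a sample of 45, with "a significance level of 5% (2-sided) and a power of 80% to demonstrate a 20% difference in rate of shunt failure". The last sentence raises the figure to 50 in each group for loss to follow-up, so 45 is read here as a per-group number.

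The section does not say which rate the 20% is measured from, which formula was used, or what loss rate was assumed. Section 2.12 names the chi-square test for categorical data, and section 2.9.1 makes shunt failure or success at 1 month the primary outcome.

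**The concern.** The rates quoted as the basis of the calculation differ by 40.9 − 15.7 = 25.2 points, but the power is claimed for 20 points. A smaller difference needs clearly more patients, so a size that is roughly right for 25.2 points cannot also give 80% power for 20.

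This is the article's only statement of how sensitive its primary comparison is. A reader who takes it at face value will believe that a true 20-point reduction in shunt failure would be missed one time in five. If it would in fact be missed about two times in five or more, a non-significant result could wrongly be taken to rule out a benefit of that size.

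**Working it through.** **Inputs, all from section 2.4:** two-sided 5% (z = 1.960), 80% power (z = 0.8416), failure rates 15.7% and 40.9%, target difference 20% (read as percentage points), 45 per group before losses and 50 after, equal groups.

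**Formulas.** Let d = |p₁ − p₂|, v = p₁(1 − p₁) + p₂(1 − p₂), and p̄ the mean of the two rates.
- Unpooled: n = (1.960 + 0.8416)² × v / d² = 7.849 × v / d²
- Pooled: n = [1.960 √(2p̄(1 − p̄)) + 0.8416 √v]² / d²
- Pooled power: Φ{[d√n − 1.960 √(2p̄(1 − p̄))] / √v}

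Exact power was obtained by enumerating all binomial outcomes for the uncorrected Pearson chi-square test.

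**Step 1: try to reproduce 45 from the quoted pair, 15.7% v 40.9%.**
- v = 0.157 × 0.843 + 0.409 × 0.591 = 0.3741; d² = 0.252² = 0.0635.
- Unpooled: 7.849 × 0.3741 / 0.0635 = 46.2, so 47.
- Pooled, with p̄ = 0.283: (1.960 × 0.6370 + 0.8416 × 0.6116)² / 0.0635 = 48.96, so 49.
- The arcsine formula gives 48; a continuity correction gives 57.
- Pooled power at 45: (0.252 × 6.708 − 1.960 × 0.6370) / 0.6116 = 0.722, so 76.5%.

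The figure of 45 is not reproduced exactly, but the closest standard formula is two patients away.

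**Step 2: try to reproduce 45 from a 20-point difference.** Here d² = 0.04.
- From the control rate, 20.9% v 40.9%: v = 0.4070. Unpooled 7.849 × 0.4070 / 0.04 = 79.9, so 80; pooled 82.6, so 83.
- From the ELD rate, 15.7% v 35.7%: v = 0.3619. Unpooled 7.849 × 0.3619 / 0.04 = 71.01, so 72; pooled 73.7, so 74.
- Pooled power at 45: (0.20 × 6.708 − 1.960 × 0.6535) / 0.6380 = 0.095, so 53.8%, from the control rate; (0.20 × 6.708 − 1.960 × 0.6180) / 0.6016 = 0.217, so 58.6%, from the ELD rate.

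**Results side by side (pooled approximation / exact chi-square for power):**

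| Rates | Difference | n per group for 80% (unpooled / pooled) | Power at 45 | Power at 50 |
|---|---|---|---|---|
| 15.7% v 40.9% | 25.2 points | 47 / 49 | 76.5% / 78.2% | 80.8% / 81.7% |
| 20.9% v 40.9% | 20 points | 80 / 83 | 53.8% / 55.6% | 58.3% / 58.7% |
| 15.7% v 35.7% | 20 points | 72 / 74 | 58.6% / 60.7% | 63.2% / 64.3% |

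**Step 3: look for a reading that rescues the sentence.**
- One-sided 5% with a 20-point difference still needs 56–65 per group without continuity correction.
- A 20% relative reduction from 40.9% (to 0.8 × 40.9 = 32.7%) needs about 545 per group.
- Reading 45 as the total (about 22 or 23 per group) lowers power to about 47% for 25.2 points and about 30–33% for 20 points.
- A 20-point gap gives 45–49 per group at rates such as 5% v 25%, but those contradict the rates quoted one sentence earlier.

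No reading tied to the quoted rates makes 45 right for a 20% difference.

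**The case against.** The strongest reply is that the sample size is sound and only a phrase is wrong. The section gives two rates and derives 45 from them. That number nearly follows from the pair: 47 by the unpooled formula, and 78.2% exact power at 45 with the chi-square test that section 2.12 names. With all 50 per group evaluable, power passes 80%. On this view the 54–61% figures describe a target that the sponsor may never have meant.

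Most of this stands, and it limits the point. A reader might infer that 45 also fails for the quoted rates, so that the trial is undersized on its own assumptions. The documents do not support that as a separate defect. The shortfall is two to four patients per group, depends on the formula, and disappears at 50. What the reply does not rescue is the sentence itself, which ties 80% power to a 20% difference.

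Two further inferences are tempting and should not be drawn:
- **That the planning rates come from outside post-hemorrhagic hydrocephalus.** The Introduction says the benefits of ELD are untested in that condition, but section 2.4 does not name the population behind its cited rates, and the source is not at hand.
- **That the exclusions after drainage in section 2.8 cut power further by a known amount.** The article gives no exclusion rate, so no figure can be attached. Nor does it state a 10% loss allowance; that is only what 45 / 0.9 = 50 implies.

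The article's silence on formula and loss rate is ordinary condensation and is not the complaint. The complaint is an explicit numerical claim that its own inputs contradict.

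**Conclusion.** The point holds as a wrong power statement. With 45 per group at two-sided 5%, power for a 20-point difference is about 54–61%, not 80%. A true difference of that size would be missed about 39–46% of the time (100 − 61 to 100 − 54) instead of 20%. Even with no losses, 50 per group gives about 58–64%. Eighty per cent power would need about 72–83 evaluable patients per group.

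The false element is most likely the 20% target and not the number of patients, because 45 lies close to what 15.7% v 40.9% requires. That attribution is an inference from the arithmetic; the article does not show its calculation.

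The figures assume that 45 is per group, that 20% means percentage points, that one of the two rates is as quoted, and that the chi-square test is used without continuity correction. With a continuity correction the requirement rises to 84–93 per group for 20 points and 57 for the quoted pair.

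**What to change.** Replace the 80%-power claim in section 2.4 with one that matches the quoted pair, for example:

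> *With 45 evaluable patients per group and a two-sided 5% level, power is about 77–78% for failure rates of 15.7% v 40.9% (about 81% if all 50 per group are evaluable), and about 54–61% for a 20-point difference.*

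Add the formula used and the loss rate behind the step from 45 to 50.

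If 20 points is truly the difference of interest, say openly that the trial has only about 54–61% power for it, and commit to not reading a null result as excluding it.

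This is a change of wording. It needs no change in enrolment. The only cost is that the stated sensitivity becomes less favourable. Keeping 80% power for 20 points would be a different decision, since it would need the 72–83 evaluable patients per group shown above, before any allowance for loss.

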### Preoperative evaluation

2.8

Repeated evaluation will be performed using the scale, as shown in Table 1, 4 days after ELD to investigate the suitability of potential LPS and then the ELD system will be removed. Patients with scores 4 will be included in this trial and the remaining patients will be excluded. Specifically, the improvement of clinical manifestation is defined as an improvement of 1 point or more in the National Institute of Health stroke scale, Glasgow coma scale, modified Rankin scale, or according to self-assessment.

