#### Primary outcome

2.9.1

The primary outcome is the shunting outcomes 1 month after surgery. Shunting outcomes include shunt failure and shunt success. According to previous studies, which is defined as the shunt obstruction, breakage, tubing exposure, malfunction, or infection requiring shunt revision. Shunt success is defined as the absence of shunt failure.

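### The step from 45 to 50 per group allows only for loss to follow-up and omits ELD patients excluded on day 4, after randomisation

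*Protocol article*

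**What the plan says.** - **Randomisation (section 2.2, Study design).** One hundred eligible patients are "randomly assigned to the ELD group (study group) and non-ELD group (control group"). Suitability for the shunt is then investigated 4 days after ELD, and this step is described for the ELD group only.
- **Day-4 rule (section 2.8, Preoperative evaluation).** Patients with the qualifying score "will be included in this trial and the remaining patients will be excluded".
- **Endpoint (section 2.9.1, Primary outcome).** "The primary outcome is the shunting outcomes 1 month after surgery". The outcome is shunt failure or its absence, so a patient who receives no shunt has no value for it.
- **Sample size (section 2.4).** The planning rates are 15.7% failure with ELD and 40.9% without. From these, 45 patients are required at 5% two-sided significance and 80% power. The last sentence of the section is: "Considering about the loss to follow-up, the sample size is enlarged to 50 for each group". I read the 45 as per group, because it is enlarged to 50 for each group.

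The text states no expected share of ELD patients without the qualifying score, no allowance for them and no replacement rule.

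**The concern.** The sample-size paragraph gives a number needed, an inflated number and the reason for the inflation. That reason leaves out a loss that the same article builds into the ELD arm. Excluded patients are a planned consequence of using ELD as a test, so they are not chance losses to follow-up, and they occur in one arm only. If a 10% loss uses the whole margin of 5 per group, nothing is left for them.

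At stake is whether 45 evaluable patients per group and 80% power describe the comparison that will be made. If the ELD arm is smaller than planned, a non-significant result could be read as ELD having no benefit when the trial had less power than it stated.

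This point concerns the evaluable number only. Two related matters are separate: the bias from selecting in one arm after randomisation, and the mismatch between the stated 20% difference and the 25.2-point gap between the cited rates.

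**Working it through.** **Inputs from the article.** Failure rates p1 = 0.157 (ELD) and p2 = 0.409 (no ELD); two-sided 5%; power 80%; 45 required and 50 randomised per group (section 2.4); 100 randomised in total (section 2.2).

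**Inputs that must be assumed.** f is the share of ELD patients without the qualifying score. The article does not give it, so I use 0 to 50%. d is loss to follow-up, taken as 10% (implied by 45/50) or 0, equal in both arms and independent of exclusion.

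**Step 1: the plan's own figures.**
- Unpooled normal approximation: n = (1.960 + 0.842)² × (0.157×0.843 + 0.409×0.591) / 0.252² = 7.849 × 0.3741 / 0.0635 = 46.2, so 47 per group. This is within 2 of the stated 45.
- The pooled version gives 49.
- Inflation: 45 / (1 − 0.10) = 50.

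The arithmetic of 2.4 is therefore close to right on its own terms, and a 10% loss uses the whole allowance.

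**Step 2: the margin.** 50 − 45 = 5. The ELD arm is below 45 as soon as exclusions plus losses exceed 5 of 50.

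**Step 3: evaluable numbers and power.** Expected evaluable ELD patients = 50(1 − f)(1 − d); controls = 50(1 − d). Power uses the two-proportion normal approximation with pooled variance under the null, at 15.7% v 40.9%:

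power = Φ{[0.252 − 1.96·√(p̄(1−p̄)(1/n1 + 1/n2))] / √(p1(1−p1)/n1 + p2(1−p2)/n2)}

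Worked example, f = 10% and d = 10%: n1 = 40.5, n2 = 45, p̄ = (40.5×0.157 + 45×0.409)/85.5 = 0.2896. The null standard error is 0.0982 and the alternative 0.0929. Power = Φ[(0.252 − 0.1926)/0.0929] = Φ(0.64) = 73.9%.

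| f | ELD v control, d = 10% | Power | P(at least 45 ELD) | ELD v control, d = 0 | Power | P(at least 45 ELD) |
|---|---|---|---|---|---|---|
| 0% | 45.0 v 45 | 76.5% | 0.62 | 50.0 v 50 | 80.8% | 1.00 |
| 5% | 42.8 v 45 | 75.3% | 0.25 | 47.5 v 50 | 79.7% | 0.96 |
| 10% | 40.5 v 45 | 73.9% | 0.07 | 45.0 v 50 | 78.4% | 0.62 |
| 20% | 36.0 v 45 | 70.7% | 0.002 | 40.0 v 50 | 75.4% | 0.05 |
| 30% | 31.5 v 45 | 66.7% | <0.001 | 35.0 v 50 | 71.6% | 0.001 |
| 50% | 22.5 v 45 | 55.6% | <0.001 | 25.0 v 50 | 60.6% | <0.001 |

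The probabilities are binomial with 50 patients and evaluable share (1 − f)(1 − d).

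**Step 4: illustration only.** Suppose ELD lowered failure purely by selecting patients, and unselected ELD patients would fail at 40.9%. Let r be the share of excluded patients who would have failed. Then 0.409 = r·f + 0.157(1 − f), so f = 0.252/(r − 0.157). With r = 1 this is 0.252/0.843 = 29.9%; with r = 0.9, 0.8 and 0.7 it is 33.9%, 39.2% and 46.4%. Under that model, f is at least about 30%.

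**The case against.** **The shortfall is not certain.** A reader might infer that the ELD arm cannot deliver 45. The article does not support that, because it gives no exclusion share. With no loss to follow-up, up to 5 of 50 could be excluded and 45 would remain. This objection stands, and the statement has to be conditional.

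**The 30% is not a minimum.** A reader might also infer that the cited rates force at least 30% exclusion. That needs ELD to act only by selection, and unselected ELD patients to fail at 40.9%. No section says either. ELD here also involves 3 days of drainage (section 2.7), and the text does not rule out an effect of drainage itself. The two rates come from a cited report that is not at hand, so the comparability of its cohorts is unknown. This stands too; the calculation is an illustration.

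**The 50 might be counted after day 4.** Section 2.8 speaks of inclusion in the trial at that point, and Figure 1 and Table 1 are not shown. But the abstract and section 2.2 recruit and randomise 100 patients before the day-4 assessment. If the later count was intended, more than 100 would be randomised and the text would still need correction.

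**The full protocol may hold a replacement rule.** It may. However, section 2.4 does state an allowance and its only reason, and that reason does not fit the design described in the same article.

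**Part of the power gap has another source.** Correct: power is already 76.5% at 45 v 45 by the pooled formula. Exclusions account only for the further drop, about 3 points at f = 10%, 6 at 20% and 10 at 30%.

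**Conclusion.** The point holds in conditional form. The allowance in section 2.4 omits the day-4 exclusions of section 2.8, so 45 evaluable patients and 80% power do not match the design. With the implied 10% loss, any exclusion takes the expected ELD number below 45. With no loss, exclusion above 10% does so. For f of 10% to 30% with 10% loss, expect 40.5 down to 31.5 evaluable ELD patients and power of about 74% down to 67%.

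These figures assume the cited rates apply to shunted patients in each arm, equal loss in both arms, and an f that is mine, not the article's. They do not show that 45 is unattainable, nor that f must be 30% or more.

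**What to change.** Rewrite the last part of section 2.4 as follows:

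1. Separate, for each arm, the number randomised from the number expected to reach the 1-month endpoint.
2. State the assumed share of ELD patients with the qualifying score, its basis and a plausible range, and state the assumed loss to follow-up separately.
3. Restate the evaluable numbers and the power over that range, in place of 45 per group at 80%.

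Alternatively, if the primary analysis is moved to all randomised patients, define the outcome for those not shunted and give planning rates and power for that denominator.

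The cost is one paragraph and a less favourable stated power. Enrolment need not change. If the sponsor prefers to keep 45 evaluable ELD patients, the number to randomise to that arm is 45/[(1 − f)(1 − d)]: with d = 10%, this is 56, 63 or 72 at f = 10%, 20% or 30%. Extra patients would restore the number but would not remove the one-sided selection after randomisation.
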